### Session Delivery and Training

The National Institute of Health’s (NIH’s) best-practice guidelines on intervention fidelity [24] will be used to develop and establish standards for virtual session delivery. This will incorporate the NIH’s framework principles: consistency in intervention content information and delivery and training the interventionist for delivering a consistent intervention. To achieve this, we will develop an interventional manual on the technology setup and troubleshooting, ground rules and videoconferencing etiquette with participants, how to maintain consistency in content delivery, techniques to engage participants and guide discussions, and the content of a checklist that will be used to assess intervention fidelity.

Second, we will provide training to the interventionists. Training sessions will occur prior to program implementation using our manual. Interim feedback will be provided after 2 and 6 sessions using fidelity checklists to maintain consistent delivery and continuous process improvement.

### Outcome Measures

#### Feasibility Outcomes

Primarily, feasibility will be measured through adherence with the SMP (defined as 80% completion). Other feasibility outcomes will include the following:

Recruitment and withdrawal rates (>80% recruitment rate and <80% withdrawal).The proportion of completed questionnaires (defined as 80% when all measures are completed) at baseline and 8 weeks post randomization in both groups.Satisfaction with the SMP as measured through questionnaires and a semistructured virtual interview with the participants following involvement in the SMP to capture the participants’ experience.Intervention fidelity (defined as consistent content and technology delivery) will be assessed by fidelity checklists and qualitative analysis of recorded video sessions after 2 sessions, 4 sessions, and at completion of all sessions to ensure that sessions are consistently delivered and as planned.

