**Methods:**

A total of 100 participants with confirmed JIA (aged 12-17 years) will be recruited from 5 Canadian pediatric rheumatology centers and randomized 1:1 to the intervention or waitlist control groups. Adolescents in the intervention group will receive the virtual SMP. Those randomized to the control group will receive standard of care alone and will later be eligible for the SMP. The SMP includes JIA disease education, self-management strategies, and peer support. Four 60- to 90-minute sessions will be conducted over 8 weeks with a group size of 4-6 participants. The primary feasibility outcome will be adherence to the SMP (defined as completion of all 4 sessions by at least 80% of participants). Other secondary feasibility outcomes will include recruitment and withdrawal rates, the proportion of completed questionnaires, engagement and satisfaction with the SMP measured through a semistructured virtual interview, and intervention fidelity (consistent content and technology delivery). Secondary preliminary effectiveness outcomes will be assessed by completing 5 validated questionnaires at pre- and postprogram time points: (1) the Medical Issues, Exercise, Pain, and Social Support Questionnaire to assess perceived ability to manage JIA (self-management); (2) the Children’s Arthritis Self-Efficacy Scale to assess self-efficacy; (3) the Pediatric Quality of Life Inventory 3.0 Rheumatology–Teen Module to assess health-related quality of life; (4) the PROMIS (Patient-Reported Outcomes Measurement Information System) Pediatric Pain Interference Scale to assess pain interference; and (5) Readiness for Adult Care in Rheumatology to assess transition readiness. Descriptive statistics and nonparametric tests will be used to analyze the data.

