### Randomization, Recruitment, and Sample Size

CONSORT (Consolidated Standards of Reporting Trials; checklist provided in Multimedia Appendix 3) 2010 guidelines suggest a sample size calculation of 9% of the anticipated full-scale RCT for the intervention group in pilot studies [22,23]. However, to establish feasibility at several sites and get an estimate of a statistically significant SD to inform a full-scale multicenter trial, our target is to conduct 2 offerings of the program with 4-6 participants per group at each of the 5 sites to control for site-specific education. Eligible participants will be identified through a review of the patient database and will be contacted by research coordinators. Some participants will also be recruited during their clinic visits. They will receive detailed information about the study, including its objectives, procedures, and potential benefits. Interested participants will provide informed consent (or assent, with parental consent for minors). The study aims to recruit a total of 100 participants. Therefore, we will require 50 participants in the intervention group and 50 in the waitlist control group. This sample size was chosen to establish feasibility and inform a larger multicenter trial. Participants will be randomized 1:1 to either the intervention group or the waitlist control group using block randomization with variable block sizes. This randomization will be conducted using REDCap (Research Electronic Data Capture; Vanderbilt University), a secure web-based application for managing data. Randomization will occur before baseline measures are completed. Participants in the intervention groups will be from the same center to adapt the program to local health care systems and account for the variability of nonformal educational practices between centers. This approach will also facilitate an evaluation/subgroup analysis of outcome measures at each center.

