## Results

### Overview

Recruitment for the VISTA-JIA study began in January 2024 and is expected to conclude by December 2025. As of March 2025, a total of 40 participants have been successfully enrolled from 5 Canadian pediatric rheumatology centers. The recruitment process involved approaching eligible participants during clinic visits and providing detailed information about the study, including its objectives, procedures, and potential benefits. Informed consent (or assent, with parental consent for minors) was obtained from interested participants.

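### The withdrawal criterion is set at below 80% withdrawal, so losing 79 of 100 participants would still meet it, and it conflicts with the pilot's other 80% targets

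*Protocol article*

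**What the plan says.** The Feasibility Outcomes section under Outcome Measures gives numerical criteria for several quantities.

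- **Recruitment and withdrawal:** "Recruitment and withdrawal rates (>80% recruitment rate and <80% withdrawal".
- **Adherence, the primary outcome:** "Primarily, feasibility will be measured through adherence with the SMP (defined as 80% completion". The abstract spells this out as "defined as completion of all 4 sessions by at least 80% of participants".
- **Questionnaires:** "The proportion of completed questionnaires (defined as 80% when all measures are completed) at baseline and 8 weeks post randomization in both groups".

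The abstract classes withdrawal as a secondary feasibility outcome. The Feasibility Outcomes paragraph of the Data Analysis Plan names withdrawal again, to be summarised descriptively, but neither repeats nor corrects the bound. No section says how the separate criteria combine into one feasibility verdict. The Significance section makes a larger trial depend on the program proving feasible and acceptable.

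**The concern.** The figure of 80% is used throughout as a level of success: 80% adherent, 80% of questionnaires complete, more than 80% recruited. Only for withdrawal is the same figure attached to a failure. This looks like a slip in which the number was kept and the direction changed.

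Feasibility is the main purpose of this pilot, and retention is one of the things a full-scale trial needs to know about. A withdrawal criterion that is met at 79% loss cannot separate a pilot that keeps its participants from one that does not. It can also report withdrawal as acceptable on the same data for which the questionnaire criterion reports failure.

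**Working it through.** **Inputs.** Total size: "The study aims to recruit a total of 100 participants". Allocation: "we will require 50 participants in the intervention group and 50 in the waitlist control group". Basis of the size: "2 offerings of the program with 4-6 participants per group at each of the 5 sites". All three come from the section on randomization, recruitment and sample size. The thresholds are those of the Feasibility Outcomes section.

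**Step 1: the plan's own figure.** Sites × offerings × group size = 5 × 2 × 5 = 50 in the intervention arm, and 2 × 50 = 100 in total. Groups of 4 to 6 give 80 to 120. The planned 100 is reproduced at the middle group size.

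**Step 2: the criterion as written.** Find the largest whole number w with w/100 < 0.80.
- 79/100 = 0.79, which passes. 80/100 = 0.80, which does not.
- The maximum is 79 withdrawn, and 100 − 79 = 21 retained.
- In one arm of 50: 39/50 = 0.78 passes and 40/50 = 0.80 does not, so 39 may withdraw and 11 remain.

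**Step 3: against the questionnaire criterion.** Assume that a participant who withdraws gives no follow-up data. Follow-up completion is then at most (100 − w)/100, and reaching 0.80 needs w ≤ 20.
- For every w from 21 to 79 the withdrawal criterion is met and the questionnaire criterion is not. That is 79 − 21 + 1 = 59 possible counts.
- At w = 79, completion is at most 21/100 = 21%.

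**Step 4: against the adherence criterion.** Count adherence in the 50 randomised to the intervention. The target needs 0.80 × 50 = 40 completers.
- With 79 withdrawals, at most 50 can be controls, so at least 79 − 50 = 29 are from the intervention arm.
- If those 29 left before completing the fourth session, adherence is at most (50 − 29)/50 = 21/50 = 42%, short of 80%.
- Adherence does not see losses from the waitlist arm. In the extreme, 10 intervention and 50 control withdrawals, 60 in all, leave adherence at 40/50 = 80% and withdrawal at 60%. Both criteria are then met as written, and only questionnaire completion (at most 40/100 = 40%) would show the loss.

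**Step 5: with the complement, below 20%.**
- Overall: 19/100 = 0.19 passes and 20/100 = 0.20 does not, so at most 19 withdraw and 81 remain. This fits a questionnaire target that allows at most 20 of 100 incomplete.
- By arm: 9/50 = 0.18 passes and 10/50 = 0.20 does not, so at least 41 of 50 (82%) remain, enough for the 40 completers that adherence needs.
- The overall figure alone would not secure this: 19 withdrawals all in the intervention arm leave 31/50 = 62%.

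**The case against.** A reader might infer that a pilot losing 79 of 100 participants would be declared feasible. The article does not support that. Adherence is primary, withdrawal is secondary, and no rule lets one criterion carry the verdict. Steps 3 and 4 show that such a pilot would miss the questionnaire target, and probably the adherence target too. This part of the objection stands and limits the point to the withdrawal criterion itself.

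The observed withdrawal rate will be reported descriptively whatever the bound, so readers can still judge retention. That also stands: what is lost is the meaning of the pass or fail label, not the data.

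The article does not say whether withdrawal means leaving the program or leaving the study. Someone who leaves the program may still answer questionnaires, which would narrow the range in step 3. That range is conditional for this reason. Step 2 does not depend on it.

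A reader might also take below 20% to be the only value that fits. It is not: a stricter bound, such as below 15% or below 10%, would also be compatible with 80% completion. Below 20% is the natural complement, but the article does not state the intended figure.

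Finally, separate criteria may legitimately give different verdicts. That does not rescue a bound that passes across nearly the whole range of possible losses. Nor is this a detail left to a fuller document: the article states the figure, and nothing in the article corrects it.

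**Conclusion.** The withdrawal bound is wrong as written. It is met with up to 79 of 100 withdrawn (39 of 50 if applied in one arm), so it has almost no power to screen. If withdrawn participants give no follow-up data, it contradicts the questionnaire target for every count from 21 to 79.

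The consequence is limited to this secondary criterion. The primary adherence criterion, the sample size and the effectiveness analyses do not depend on it, and the overall feasibility verdict does not follow from it. The figures assume that the planned 100 are randomised at 50 per arm. That below 20% was intended is an inference from the other 80% targets.

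**What to change.** Change the withdrawal criterion to below 20% withdrawal, equivalently above 80% retention, after the sponsor has confirmed that this was the intended value. Define it as withdrawn divided by randomised, and report it overall and by arm, because adherence gives no information on losses from the waitlist group. Make the correction, with its date, before results are known; recruitment was still open when the article was published.

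The cost is one line of text, with no change to sample size, data collection or analysis. The downside is that the criterion becomes stricter: it fails at 20 withdrawals of 100, where the present one fails only at 80.

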## Methods

### Study Design

A pilot RCT will be conducted to determine the feasibility and preliminary effectiveness of a virtual SMP intervention. Eligible participants will be randomized 1:1 to either the intervention group or a waitlist control group. Both groups will complete baseline measures (T0) as well as postprogram measures (T1). Participants enrolled into the intervention will undergo the SMP and be asked to participate in an optional postintervention interview. The waitlist control group will continue receiving standard of care during this program period. They will be given the option to complete the SMP afterwards, and if completed, be asked to complete postintervention questionnaires. They will also be asked to participate in the optional postintervention interview. The study is registered in ClinicalTrials.gov (NCT06184100). Figure 1 shows the trial schema, and Multimedia Appendix 1 shows the timeline. This study follows the SPIRIT (Standard Protocol Items: Recommendations for Interventional Trials; checklist provided in Multimedia Appendix 2) guidelines.

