### Intervention

The program consists of JIA disease education, self-management strategies, and peer support in a group-based setting. Four sessions, 60-90 minutes each, will be conducted over 8 weeks with a group size of 4-6 participants via videoconferencing platforms. Each session will include Microsoft PowerPoint–delivered presentations, interactive activities, and group discussions. The 4 sessions will focus on the following themes: Overview and Diagnosis of JIA, Daily Living and Exercise, Coping Strategies, and Medication and Lifestyle Management. To ensure intervention fidelity, sessions will be provided by the same designated health care professionals. All sessions will be video-recorded and uploaded to a secured research server to assess the group’s dynamic and ensure sessions are delivered as planned (fidelity). Young adults living with JIA from participating centers will be asked to sit in during these sessions to share their lived experiences and foster peer social support. Additionally, each site will include site-specific resources. After completing the intervention, participants will be asked to independently attend an optional semistructured interview to capture participant experiences of the intervention.

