#### Preliminary Effectiveness Measures

Participants of both the intervention and control groups will complete 5 validated and reliable patient-reported outcome measures on the web at baseline and post program. This includes the following:

The Medical Issues, Exercise, Pain, and Social Support Questionnaire—a validated (eg, concurrent validity and construct validity) and reliable (eg, internal consistency) measure for perceived ability (eg, knowledge, skill, behavior, attitudes, and self-efficacy) to manage JIA [25].The Children’s Arthritis Self-Efficacy Scale—a validated (eg, concurrent validity and construct validity) and reliable (eg, internal consistency) measure for arthritis self-efficacy [26].The Pediatric Quality of Life Inventory 3.0 Rheumatology–Teen Module—a validated (eg, construct validity and concurrent validity) and reliable (eg, internal consistency) measure used for pediatric rheumatology–specific health-related quality of life in children aged 13-18 years [27].The PROMIS (Patient-Reported Outcomes Measurement Information System) Pediatric Pain Interference Scale—a validated (eg, concurrent validity and construct validity) and reliable (eg, internal consistency) measure for pain behavior in children aged 8-17 years [28].Readiness for Adult Care in Rheumatology—a validated (eg, concurrent validity and construct validity) and reliable (eg, internal consistency) measure to assess transition readiness in adolescents with JIA [29].

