#### Data Analysis Plan

##### Feasibility Outcomes

The feasibility of the SMP will be analyzed using descriptive statistics (eg, mean, SD, and frequencies) based on (1) adherence with the SMP (defined as 80% when the participant completes 4 sessions over 8 weeks), (2) recruitment and withdrawal rates, and (3) the proportion of completed questionnaires at baseline and 4 weeks after the last session (defined as 80% when all measures completed).

This study will use qualitative thematic analysis [30,31] to analyze the data. The experiences, perceptions, and satisfaction measured through video-recorded semistructured individual interviews will be transcribed verbatim and entered to a data analysis software (NVivo version 12.0; Lumivero) [32] for analysis. This method involves iterative cycles of coding, interpreting, and reflecting on the data to identify patterns and themes that capture participants’ experiences and perceptions of SMP. Key nonverbal cues, terms, and phrases will be noted and underlined in the transcript and coded accordingly. All qualitative data will be read separately several times by the research assistant and at least 2 investigators to obtain an overall understanding of the data, generate initial codes, and develop themes based on research questions. The themes will be refined, defined, and supported by extracts from the transcript. Finally, the themes will be documented in a manuscript.

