##### Preliminary Effectiveness Outcomes

The quantitative data will be entered into SPSS [34]. Descriptive statistics will be used to analyze the patient-reported outcome measures with an ordinal Likert scale at baseline and immediately post intervention. In addition, nonparametric Wilcoxon signed rank tests will be used to assess if there is a significant difference between a pre- and posttest outcome. Nonparametric tests will be used due to the small sample size and a lack of normally distributed data. Changes in pre- and posttest outcomes will be analyzed over time using a repeated measures mixed linear model approach where participants will be included as the random effect and baseline scores, study site, and disease-related characteristics will be used as fixed factors or covariates.

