### Session Delivery and Training

We have developed and established standards for virtual session delivery based on the NIH’s best-practice guidelines on intervention fidelity. This incorporates the NIH’s framework principles: consistency in intervention content information and delivery and training the interventionist for delivering a consistent intervention. Training sessions for the interventionists have been conducted. One education intervention has been conducted and will be used to further improve the program.

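### The single post-programme assessment T1 has three conflicting timings; one can fall before the programme ends, and two give no explicit date for the waitlist arm

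*Protocol article*

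**What the plan says.** The Study Design section provides for one baseline (T0) and one postprogram measurement (T1), completed by both groups. Elsewhere the same questionnaires are timed as follows.

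- Outcome Measures, Feasibility Outcomes: questionnaire completion is assessed "at baseline and 8 weeks post randomization in both groups".
- Data Analysis Plan, Feasibility Outcomes: the criterion is "the proportion of completed questionnaires at baseline and 4 weeks after the last session".
- Preliminary Effectiveness Outcomes: the measures are analysed "at baseline and immediately post intervention".
- Preliminary Effectiveness Measures: both groups complete the "patient-reported outcome measures on the web at baseline and post program", with no number of weeks.

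Three statements bear on which of these can be met. On the programme: "Four sessions, 60-90 minutes each, will be conducted over 8 weeks with a group size of 4-6 participants". On the order of events: "Randomization will occur before baseline measures are completed". The Randomization, Recruitment, and Sample Size section adds that each intervention group is formed within one centre. The article does not give the interval from randomization to session 1, and does not say whether allocation is rolling or done in batches.

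**The concern.** This is a contradiction in the current text, not detail left to a fuller document. T1 carries all five effectiveness outcomes and the questionnaire-completion criterion. The pilot is also meant to supply an SD for the full-scale trial.

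Two separate risks follow, one from each way of timing T1. If week 8 after randomization is used, both arms are measured at the same time, but some intervention participants may still be in the programme or waiting for it, which would pull any difference towards zero. If T1 is tied to the last session or the end of the intervention, it follows the programme. The waitlist arm, however, has no last session before T1 and is given no date, so its interval from T0 to T1 may differ from that of the intervention arm.

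**Working it through.** **The plan's own figure.** 5 sites × 2 offerings × 5 per group = 50 intervention participants, and 1:1 allocation gives 100, as stated. Groups of 4 or 6 would give 40 or 60 in the intervention arm.

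**The three timings on one scale.** Let L be the weeks from randomization to session 1, and S the weeks from session 1 to session 4. The article says four sessions over 8 weeks. I take S = 8, or S = 6 if sessions come every 2 weeks (an assumption). In weeks from randomization:

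- A (8 weeks post randomization) = 8
- B (4 weeks after the last session) = L + S + 4
- C (immediately post intervention) = L + S

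| S | L | A | B | C |
|---|---|---|---|---|
| 8 | 0 | 8 | 12 | 8 |
| 8 | 4 | 8 | 16 | 12 |
| 6 | 0 | 8 | 10 | 6 |
| 6 | 4 | 8 | 14 | 10 |

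B − C = 4 always. A = B would need L + S = 4, which is impossible with S of 6 or 8. A = C only if L + S = 8. No schedule meets all three, and the two timings of the completion criterion (A and B) never agree. A falls before the last session when L > 0 (S = 8) or L > 2 weeks (S = 6). T0 has to be completed after randomization, and a group has to be assembled, within that margin.

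**How long L might be.** The article does not say. Assume rolling randomization, even accrual over sites and time, enrolled meaning randomized, and a group that starts when full.

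- Planned pace: 100 / 24 months / 5 sites / 2 arms = 0.417 intervention participants per site per month, or one every 2.4 months. In a group of five the first waits 4 × 2.4 = 9.6 months. The mean wait is (9.6 + 7.2 + 4.8 + 2.4 + 0) / 5 = 4.8 months, about 21 weeks. For groups of 4 and 6 the means are 3.6 and 6.0 months.
- Reported pace (Results, Overview): 40 / 15 months / 5 / 2 = 0.267, or one every 3.75 months. The mean wait for a group of five is 2 × 3.75 = 7.5 months.

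A simulation with random arrivals, blocks of 2 and 4, groups of 4 to 6 and a set-up time of 0 or 2 weeks (all assumptions except group size) gives the following shares of intervention participants at week 8.

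| Pace | Not finished | Not started |
|---|---|---|
| Planned, S = 6 | 71–84% | 59–76% |
| Planned, S = 8 | 75–100% | 59–76% |
| Reported, S = 6 or 8 | 73–100% | 66–79% |
| Four times planned, S = 6 or 8 | 59–100% | 15–49% |

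The 100% values arise by construction, because S = 8 plus any set-up time puts everyone past week 8.

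**The other case.** With batch randomization and an immediate start, L = 0. The last session then falls at week 6 or week 8, and A does not precede it.

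**The case against.** The strongest reply is that the effectiveness timing is more consistent than it looks. The Abstract, Study Design, Preliminary Effectiveness Measures and Preliminary Effectiveness Outcomes all place those measures after the programme. The week-8 and 4-week timings are attached to a feasibility outcome. Dilution of the effect therefore needs the week-8 timing to override four other statements. This stands: dilution is a risk, not the stated effectiveness plan. It does not remove the conflict, because the questionnaires are the same and the design has only one T1.

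Second, Study Design keeps controls on standard care during the programme period and offers them the programme afterwards, which implies an anchor. This also stands in part: the anchor is implied, but no date or window is given.

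Third, the waiting times rest on rolling randomization. The article mentions only block randomization with variable block sizes. Patients are identified partly by database review, so a site could contact a cohort together. The trial schema and timeline, not shown here, may state a schedule, though they could not remove the conflict in the text.

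A reader might also infer from the progress report (40 enrolled, yet "One education intervention has been conducted and will be used to further improve the program") that most allocated intervention participants were still untreated in March 2025. The article does not support that count: enrolled is not stated to mean randomized, and the one delivery is neither defined nor dated.

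Finally, the primary outcome is adherence to the programme, which T1 timing does not touch.

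**Conclusion.** The contradiction holds without any assumption about accrual: T1 has three timings, two of them always 4 weeks apart. For S of 6 or 8 weeks, the two timings of the completion criterion cannot coincide. That a T1 at week 8 can precede programme end follows from the 8-week programme and the order of randomization, T0 and group formation. That most intervention participants would be unfinished by then (71% or more at the planned pace) holds only under rolling randomization and the other stated assumptions.

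A reader might infer that T1 will fail to measure the programme and will also differ by arm. The document does not support that. The two consequences belong to different readings: the week-8 timing is common to both arms, and the other two follow the programme. Each is a possible consequence of the timing chosen, and neither is certain. The effect is confined to secondary outcomes, namely questionnaire completion and preliminary effectiveness, and to the SD carried forward.

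**What to change.** Put one T1 definition in both Feasibility Outcomes sections and in Preliminary Effectiveness Outcomes: a fixed window (for instance 0 to 2 weeks) after the last session of the site's offering. Apply it on the same calendar dates to the waitlist participants matched to that offering, before they start the programme. State in advance how they are matched, for example by order of randomization within the centre.

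For every participant, including those already enrolled, record the intervals from randomization to session 1 and from T0 to T1. Run a sensitivity analysis on the T0–T1 interval, for example by adding it to the planned mixed model.

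The cost is protocol wording and questionnaire scheduling. The downside is that the T0–T1 interval will vary between offerings and has to be reported.

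Batch randomization by site is an option for the full-scale trial, not a required change here. With 40 already enrolled it would alter the procedure mid-trial, and it only moves the wait to before randomization. Holding consent until 8 to 12 adolescents are available, at 100 / 24 / 5 = 0.83 per site per month, keeps the first one waiting 7 / 0.83 to 11 / 0.83, or about 8 to 13 months.
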